#### **Patient reported outcome measures**

As part of this study, we will be using two PROM questionnaires.

The Kansas City Cardiomyopathy (KCCQ) questionnaire has been extensively validated to assess health status and quality of life in patients with a range of cardiomyopathies(71-74). It consists of 23 questions and has a recall period of 2 weeks over which patients describe the frequency and severity of their symptoms, their physical and social limitations, and how they perceive their symptoms to affect their quality of life. These domains can be combined into an Overall Summary score that combines the Total Symptom, Physical and Social Limitation, and Quality of Life scales to provide a more holistic summary of the patients' health status.

A second questionnaire will be used to screen for possible side effects following MR-guided radiotherapy to the stellate ganglia. We have designed this questionnaire by compiling symptoms that are commonly reported in trials of surgical sympathetic denervation(42, 43), and patients receiving treatment for head and neck cancers(75)

#### **Biomarker Measurements:**

The project will initially focus on plasma NPY levels, which we have significant experience of measuring. However, as other targets are identified from on-going studies then further biomarker measurements may

be made as required. Blood samples will be taken from a peripheral vein. Blood samples will be transported to the lab in secure containers on dry ice by a member of the study team. Here they will be centrifuged and immediately frozen to -80 °C. NPY levels will be measured using ELISA (EZHNPY-25K, Millipore) as described previously (31, 32, 76, 77).

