### Visits 4 to 6 – Hypofractionated radiotherapy to the stellate ganglia

Over the course of one-week, patients will undergo up to 3 fractions of hypofractionated radiotherapy targeted bilaterally to the lower half of the stellate ganglia and T1-2 paravertebral chain (60 minutes).

Prior to each fraction of radiotherapy blood samples (approximately 16 ml) will be taken to monitor plasma levels of NPY and other biomarkers. Routine blood tests (including renal function, full blood count and thyroid function) will also be checked prior to the first fraction of treatment. Blood samples will be labelled with the participants' study number and stored for analysis. All stored samples will be de-identified and will only be identified by a study specific participant number and will be destroyed after processing, unless participants have specifically consented to have their samples stored for use in future studies (10 minutes)

Before and after each fraction of radiotherapy a cardiovascular examination and neurological examination will be performed by one of the study doctors paying attention to signs of Horner's syndrome

(ptosis and pupil constriction) or upper limb sensory impairment. Cardiovascular observations including postural blood pressures and heart rate will be recorded, and an electrocardiogram will be performed. New postural hypotension defined as a symptomatic postural blood pressure drop of 20mmHg will be considered significant. (10 minutes each) If any serious treatment related adverse events are detected, then no further fractions of radiation will be delivered to that patient.

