### **9.7. Sample Handling**

A total of 6 samples (total volume of no more than 100 ml) will be collected during the entire study duration. Blood samples will be stored in the research facility in OCMR until processed. All stored samples for this study will only be identified by a study specific participant number and will be destroyed after processing, unless participant has given consent for use of samples in future studies when signing the consent form. All processing of these blood samples will be performed in Oxford University Laboratories, either at the John Radcliffe Hospital, or the Department of Physiology Anatomy and Genetics and will be performed by the University Research Team. Blood samples will be transported to the lab in secure containers on dry ice by a member of the study team. Here they will be centrifuged and immediately frozen to -80 °C. NPY levels will be measured using ELISA (EZHNPY-25K, Millipore) as described previously (31, 32, 76, 77).

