#### **11.2. Description of the Statistical Methods**

To measure our primary safety endpoint, we will measure the frequency of adverse events in the 6 months post radiotherapy. Our trial is powered to detect adverse event rates of 34% (see below)

For secondary outcome measures such as changes in circulating biomarker levels (NPY) and changes in number of device therapies following radiotherapy we will use non-parametric tests such as a Wilcoxon signed rank test to determine if changes are statistically significant.

To assess correlation between changes in biomarker levels and number of device therapies we will use a correlation matrix using non-parametric correlation tests such as Spearman rank-order correlation.

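### As written, blood travels on dry ice before it is centrifuged, so whole blood would freeze before the plasma for the NPY outcome is separated

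*Protocol*

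**What the plan says.** The biomarker text in Protocol Section 9.4.2 names the analyte and the matrix: "The project will initially focus on plasma NPY levels, which we have significant experience of measuring". It then gives the steps in order. Collection: "Blood samples will be taken from a peripheral vein". Transport: "Blood samples will be transported to the lab in secure containers on dry ice by a member of the study team". At the laboratory: "Here they will be centrifuged and immediately frozen to -80 °C".

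Section 9.7 (Sample Handling) repeats the transport and centrifugation sentences. It adds one sentence that Section 9.4.2 does not contain: "Blood samples will be stored in the research facility in OCMR until processed". That sentence gives no temperature, and it does not say whether any separation happens during storage.

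Section 9.6 ties the samples to plasma NPY at the treatment visits: "Prior to each fraction of radiotherapy blood samples (approximately 16 ml) will be taken to monitor plasma levels of NPY and other biomarkers". It asks for the same at the three safety visits. Section 11.2 then uses the results: "For secondary outcome measures such as changes in circulating biomarker levels (NPY) and changes in number of device therapies following radiotherapy" are to be examined with non-parametric tests such as the Wilcoxon signed rank test, and changes in biomarkers are to be correlated with device therapies by a method such as Spearman's.

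**The concern.** Plasma has to be separated from the cells while the blood is still liquid. Blood that is frozen unspun and later thawed contains lysed cells and platelets, and a spin at that stage no longer separates plasma from intact cells. The written order puts dry ice before the spin, so it does not yield the analyte that the protocol names.

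Change in NPY is a secondary outcome and one side of the biomarker-arrhythmia correlation. It also bears on two of the four research questions in Section 5(b). With 13 patients there is little room to absorb measurement error, and a sample frozen before separation cannot be recovered later.

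**Working it through.** No test, rate or sample-size formula is involved. The check sets the handling text side by side and then counts the samples exposed.

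**Order of the steps**

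| Step | Section 9.4.2 | Section 9.7 |
|---|---|---|
| Draw | Peripheral vein; no spin stated | Collection stated; no spin stated |
| Storage before processing | Not mentioned | At OCMR; no temperature or spin given; not placed in order relative to transport |
| Transport | Dry ice | Dry ice |
| Centrifugation | At the laboratory, after transport | At the laboratory, after transport |
| Freezing to -80 °C | Directly after the spin | Directly after the spin |

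**Is there a spin before transport anywhere else?** The descriptions of visit 1 (Section 9.5), visits 4 to 6 and visits 7 to 9 (Section 9.6), and the schedule in Appendix A were checked. None mentions centrifugation or separation of plasma before transport. The assay references in both sections are attached to the sentence on the ELISA measurement, not to the transport sentence.

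**What the order implies.** Dry ice is at about -78 °C. This is a general physical fact, not a figure from the protocol. It is practically the temperature of the freezer that the samples go into after the spin. Whole blood carried on it would therefore already be frozen on arrival. The next step, a spin followed at once by freezing, only makes sense for liquid blood. The two sentences do not fit together.

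**Samples exposed**

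- Section 9.7 gives a total of 6 samples per patient. Section 9.6 describes NPY sampling at visits 4, 5, 6, 7, 8 and 9, which is also 6. With 13 patients: 6 x 13 = 78.
- Appendix A marks laboratory tests at visits 1, 4, 5, 6, 7, 8 and 9, which is 7. With 13 patients: 7 x 13 = 91.
- At about 16 ml per draw, 6 x 16 = 96 ml falls within the 100 ml ceiling in Section 9.7, and 7 x 16 = 112 ml does not. This favours 78. However, the objectives table in Section 6 also names an initial visit for the biomarker comparison, so a seventh NPY sample cannot be excluded.

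On either count, the share of NPY samples covered by the faulty order is all of them.

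**The case against.** The strongest reply is that this is a slip of the pen and not how the laboratory works. The matrix is named as plasma, the team states experience with the assay, and spinning on arrival presupposes liquid blood. The transport and centrifugation sentences are the same in both sections, which suggests that one error was copied. Staff may already spin first, or carry unspun blood on another coolant. All of this is plausible. It changes the likely cause, but not the fact that the only procedure shown gives the wrong order.

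A reader might also infer more than the text supports:

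- **That the order was chosen deliberately because it appears twice.** Identical wording is equally well explained by copying.
- **That the NPY results would be worthless.** The documents give no data on how the assay performs in such samples. What can be said is that the measurement would not be a valid measurement of plasma NPY.
- **That both sections place storage at OCMR ahead of transport.** Only Section 9.7 mentions storage, and it does not place it in the sequence.
- **That differences between sites bias the before-after comparison.** Section 9.4.1 describes two treatment platforms at different providers, but the protocol does not say where blood is drawn at the treatment visits or at the first two safety visits. Such bias is a possibility, not a documented defect.
- **That the absence of tube type and draw-to-spin limits is an error.** Those details can properly sit in a laboratory SOP.

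It also stands that the effect is confined to one secondary biomarker and its correlation.

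**Conclusion.** The point holds as an error in the written procedure. Followed literally, Sections 9.4.2 and 9.7 freeze whole blood before plasma is separated. The NPY assay would then run on freeze-thawed, lysed blood, and neither the NPY secondary outcome nor its correlation with device therapies would be validly measured. All NPY samples are affected: 78 by Section 9.7, or up to 91 if the visit 1 draw counts.

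The conclusion rests on two assumptions from outside the documents: the temperature of dry ice, and the ordinary laboratory fact that freezing and thawing lyses blood cells. The size of the resulting assay error is not given and is not estimated here. The primary safety endpoint, the dose-escalation decisions and the sample size of 13 do not depend on these samples. The correction is worth making before further samples are taken, but it does not threaten the trial's main purpose.

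**What to change.** Correct the handling sentences in Sections 9.4.2 and 9.7 so that they give one order. Blood is centrifuged and plasma separated before any freezing or dry-ice transport, and dry ice is used only for separated, frozen plasma. If spinning where blood is drawn is not practical, state instead that unspun blood travels unfrozen to the laboratory and is spun there before freezing. Say in Section 9.7 whether storage at OCMR comes before or after separation. State that the same handling applies at every visit, so that samples compared within a patient are treated alike.

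The cost is a few sentences in the protocol and a matching laboratory SOP, where tube type and time limits can be set. The small practical downside is the need for centrifuge access, or a prompt unfrozen transfer, from each place where blood is drawn.

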## **9.5. Baseline Assessments**

### **Visit 1 – screening visit and screening 1.5 T MRI**

Eligibility of participants will be re-checked by pre-defined inclusion/exclusion criteria (see 6.2 and 6.3 for details) by the study team and MRI safety checks will be conducted. Written informed screening consent will be obtained by GCP trained investigators or research nurses who have also been trained to obtain consent for the study and procedures and listed on the study delegation log (20 minutes).

Anthropometric measurements such as height, weight, BMI will be recorded, and routine cardiovascular examination will afford the detection of any previously undiagnosed pathology that may have implications for safety. Participants will be asked to complete the Kansas City Cardiomyopathy Questionnaire (KCCQ) so assess baseline quality of life scores. Standard 12 lead electrocardiogram will be taken, which is a highly routine test, and baseline blood tests will be taken (approximately 16ml) (10 minutes)

A 1.5 T Cardiac Magnetic Resonance (CMR) scan will be performed on a 1.5 Tesla MR scanner at the OCMR with sequences optimised to minimise device related artefact to allow us to clearly visualise the stellate ganglia and heart. Participants will lie in a supine position and a dedicated coil will be placed around their chest, neck and head. Oxford University Hospitals NHS Foundation Trust has a standard operating procedure in place (developed with the Chief Investigator) for MR imaging of patients with implantable cardiac devices and this will be adhered to. The expected magnetic resonance imaging time is less than 60 -90 minutes. There is a scheduled 5–10-minute break during scanning.

We anticipate a 20-30% screening failure so we will not proceed with formal study consent until eligibility is confirmed following screening assessment. Patients who pass screening will be invited to formally enrol into the study and will proceed as outlined below. Patients who fail screening will exit at this point.

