A dose escalation protocol will be used to determine the lowest radiotherapy dose that can safely achieve sympathetic downregulation. This protocol will involve 13 patients with the doses escalated as follows: The first 3 patients would be treated at 8 Gy per fraction for 3 fractions on alternate days. If no serious adverse events occur then we will increase the dose to 9 Gy per fraction for 3 fractions on alternate days in the next 3 patients, 10 Gy per fraction for the next 3 patients for 3 fractions on alternate days and 11 Gy per fraction for 3 fractions on alternate days for the final 4 patients (figure 2). There will be a minimum of 6 weeks between the last participant treated at each dose before escalation the next dose to allow for detection of adverse events at participants' 6 week follow up visit. Before each dose escalation we will have an independent safety committee review all patient data and radiotherapy doses will only be escalated if there are no safety concerns.

Our study is a safety study, and we are powered to detect serious adverse events as our primary endpoint. Serious adverse events (SAEs) defined as any related and unexpected grade 3 toxicity requiring hospitalization, grade 4 toxicity or grade 5 toxicity as defined by the common terminology criteria for adverse events.

If a serious adverse event occurs, then no further fractions would be given to that patient and the dose would be reduced by 1 Gy for all subsequent patients (up to a total of 13 patients) without further dose escalation. If an SAE occurs at the lowest radiotherapy dose (8 Gy per fraction for 3 fractions) all subsequent patients will receive treatment at the even lower dose of 7 Gy per fraction for 3 fractions, if approved by our independent safety committee. However as highlighted in section 5 we have chosen a starting dose within the safe upper limit for neuronal tissue, so we do not anticipate this. An early stopping rule will be set to halt enrolment if 4 out of the first 8 patients develop and SAE. If patients withdraw from this trial then they will be replaced, and the study will continue until 13 patients have completed the dose escalation protocol (as detailed in section 9.8). We will not recruit any extra participants into our dose escalation protocol, unless participants withdraw, in which case they will be replaced. Once 13 participants complete the dose escalation protocol no further patients will be recruited.

Figure 2.

[figure not shown]

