### 8.2. Inclusion Criteria

#### General Inclusion Criteria

- Participant is willing and able to give informed consent for participation in the study.
- Male or Female, aged at least 18 years old.
- Known diagnosis of structural heart disease defined as any patient with impaired left ventricular ejection fraction (less than 55%) due to any cause including ischaemic cardiomyopathy, dilated cardiomyopathy, hypertrophic cardiomyopathy or Arrhythmogenic cardiomyopathy.
- CMR compatible ICD device implanted a minimum of 6 months ago, under follow-up at Oxford University Hospitals NHS Foundation Trust.
- Experienced more than one appropriate ICD therapy (shocks or ATP) for ventricular arrhythmia in the last 6 months
- Established on optimal guideline based medical therapy for heart failure and arrhythmia

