## **9. PROTOCOL PROCEDURES**

### **9.1. Recruitment**

Patients attending outpatient heart failure or arrhythmia clinics, under existing follow-up in pacing clinic, or admitted as an in-patient under the electrophysiology team will be identified by their routine clinical care team. Either a letter of invitation along with the Patient information leaflet (PIL) will be sent ahead of their clinical appointment along with the appointment letter, or the clinical team will inform the patient on the day of their clinical appointment (a routine appointment in the heart failure clinic or in the in the arrhythmia/pacing clinic, or during their in-patient admission) about the study. Potential participants who express an interest in participation will be offered the opportunity to discuss the study with the study team and with their agreement, their contact details can be provided by the clinical team to the study team. Potential participants will be allowed at least 24 hours to consider the written and verbal study information before entering the study. The informed consent document will be signed at the first study visit by the participant and delegated study investigator.

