## 9.6. Subsequent Visits

### Visit 2 – Radiotherapy team visit and study consent

Once Participants have been screened, they will be invited to formally enrol into the study. This process will begin with an introductory visit with the radiotherapy team. At this point patients will receive additional counselling about the radiotherapy process and possible side effects. This visit will last approximately 1 hour. If patients are still happy to proceed with the study, then written informed consent will be obtained at this point.

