#### Visits 7 to 9 – safety visits

Over the course of 6 months post completion of hypofractionated radiotherapy, patients will be followed up to monitor for treatment related adverse events and to monitor biomarker response. This will comprise 3 further study visits at 6 weeks, 3 months and 6 months (or earlier if clinically indicated) following completion of radiotherapy.

During each study visit, blood samples will be taken (approximately 16 ml) to monitor plasma levels of NPY and other biomarkers. At the final 6-month study visit (or earlier if clinically indicated) routine blood tests will also be repeated (as detailed above).

Participants will be interviewed to assess for side effects from their radiotherapy and cardiac sympathetic denervation. Physical examinations and observations will be performed, and an electrocardiogram will be taken (as detailed above). Participants will also be asked to complete the KCCQ and a symptom questionnaire to screen for any side effects from their radiotherapy or cardiac sympathetic denervation.

At the 6 months visit a final 1.5T CMR scan will also be performed at OCMR to reassess cardiac function and stellate ganglia anatomy (as detailed above).

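### The only pre-treatment KCCQ is taken at screening, with no stated limit on the time to the first fraction, so any change in between can be counted in the post-radiotherapy KCCQ change

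*Protocol*

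**What the plan says.** **Baseline.** Protocol section 9.5 (Visit 1) says: "Participants will be asked to complete the Kansas City Cardiomyopathy Questionnaire (KCCQ) so assess baseline quality of life scores". The KCCQ row of Appendix A marks the screening visit and Visit 9, with nothing at Visits 2 to 6.

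**What is measured at treatment start.** Section 9.6 (Visits 4 to 6) takes biomarker blood before each fraction, and an examination and ECG before and after each one. Appendix A also marks the symptom questionnaire at Visit 4.

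**After treatment.** Section 9.6 (Visits 7 to 9) covers 6 weeks, 3 months and 6 months, and states: "Participants will also be asked to complete the KCCQ and a symptom questionnaire to screen for any side effects". Section 6 gives the KCCQ timepoint as monitoring visits up to 6 months. Appendix A marks only Visit 9 after treatment.

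**Time from Visit 1 to Visit 4.** No window is given. The radiotherapy consultation and consent (Visit 2) and the planning scans (Visit 3) come in between. Section 7 adds, at each dose step: "There will be a minimum of 6 weeks between the last participant treated at each dose before escalation the next dose". Sections 10.1 and 13.3 suspend recruitment and radiotherapy during a safety review, with no stated length.

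**Who is screened.** Eligibility in section 8.2 reads: "Experienced more than one appropriate ICD therapy (shocks or ATP) for ventricular arrhythmia in the last 6 months". Section 9.1 recruits from heart failure and arrhythmia clinics and pacing follow-up, and also takes patients "or admitted as an in-patient under the electrophysiology team". The KCCQ "has a recall period of 2 weeks over which patients describe the frequency and severity of their symptoms" (section 9.4.2).

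**Status and analysis.** The KCCQ is a secondary outcome under the feasibility objective, and the synopsis states that there is no comparator. Section 11.2 offers the Wilcoxon signed-rank test as an example for secondary outcomes and names NPY and device therapies. It names no KCCQ contrast or test.

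**The concern.** In an uncontrolled series the before-after change is the only evidence of effect, so the baseline has to describe the patient at the start of treatment. Here it describes the two weeks before screening, and the time from screening to treatment is open-ended. Whatever happens to health status in that interval is added to the change after radiotherapy and cannot be separated from it.

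The selection of patients gives a reason to expect some upward movement. Entry requires more than one appropriate device therapy within six months, and some patients will be found during an admission. A patient who completes the KCCQ soon after such an episode may score low and then improve before the first fraction without any study treatment. At stake is how far the quality-of-life result can be read as an effect of radiotherapy. A score that was not collected at Visit 4 cannot be recovered at analysis.

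**Working it through.** The protocol states no figure for this point, so there is none to reproduce. The check has two parts.

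**1. What the schedule fixes**

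| Measure | Visit 1 | Visit 4 (first fraction) | After treatment |
|---|---|---|---|
| Bloods, ECG, examination | yes | yes | Visits 7, 8, 9 |
| Symptom questionnaire | no | yes | Visits 7, 8, 9 |
| KCCQ | yes | no | Visits 7 to 9 in the section 9.6 text; Visit 9 only in Appendix A |

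Write the follow-up change as (follow-up − Visit 1) = (Visit 4 − Visit 1) + (follow-up − Visit 4). The first bracket is entirely untreated. With no KCCQ at Visit 4 it is unobserved, and with no control group it cannot be estimated in any other way. Its mean is the bias from the placement of the baseline, and it may be positive or negative.

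The KCCQ recalls 2 weeks, while the qualifying therapies may be up to 6 months (about 26 weeks) old. The screening score overlaps the qualifying episode only in patients screened soon after it.

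**2. Illustration of size, with assumed inputs**

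From the protocol: n = 13. Assumed: SD of KCCQ change 15 or 20 points; untreated improvement (drift) of 5 or 10 points in k of the 13 patients; no treatment effect; Normal changes; Wilcoxon signed-rank test, two-sided 5%, counting only results in the direction of improvement.

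Mean bias = k × drift / 13.
- All 13 drift: 5 to 10 points.
- 3 or 4 drift: from 3 × 5/13 = 1.2 points to 4 × 10/13 = 3.1 points.

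With n = 13 the exact test declares improvement when the sum of negative ranks is 17 or less. Under no drift that has probability 2.4%. Simulated chance of a falsely significant improvement (200,000 trials per cell):

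| Patients drifting | SD 15, drift 5 | SD 15, drift 10 | SD 20, drift 5 | SD 20, drift 10 |
|---|---|---|---|---|
| all 13 | 19% | 57% | 12% | 36% |
| 4 of 13 | 4.8% | 8.1% | 4.1% | 6.4% |
| 3 of 13 | 4.0% | 6.1% | 3.6% | 5.0% |

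Runs of 4,000 trials per cell agree within simulation error. Across runs the ranges are about 12% to 58% when everyone drifts and about 3% to 8% when three or four do. With a drift of only 3 points in all 13 patients the chance is 9% (SD 15) or 7% (SD 20).

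A downward drift of the same size gives the same bias with the opposite sign and would hide a benefit.

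**The case against.** A reader might infer that the baseline is taken at the low point of the illness, and that recovery from the index arrhythmia will therefore be scored as benefit. The documents do not support that.

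- Qualifying therapies may be up to 6 months old against a 2-week recall, and no single index event is defined.
- In-patients are one recruitment route among several, with no share stated. Even they have at least 24 hours to consider and are then invited to a separate screening visit, which need not fall within two weeks of the event.
- The 6-week hold applies at dose steps. It lengthens the interval only for someone screened around one, and the protocol does not say whether screening continues during a hold.
- Drift could be downward. Section 9.4.1 describes a particularly poor prognosis, with mortality above 50% at 5 years.
- No KCCQ test or success criterion is stated, and the KCCQ plays no part in the primary endpoint, dose escalation or stopping rule.
- The higher simulated figures require every patient to improve by 5 to 10 points before treatment.

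All of this stands and limits the claim to a possible bias of unknown size and direction. Some support for upward drift remains. Section 7 describes patients who recently needed device therapy. Section 8.1 expects to find patients through remote monitoring, device clinics and acute admissions, and to draw on those having VT ablation, whose recovery could fall in the same interval.

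The objection does not remove the gap in the schedule. Nor is this a matter for a later analysis plan: assessment times are set in the protocol, and section 11.1 says there is no separate plan.

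**Conclusion.** The point holds as a weakness in the timing of a secondary outcome. The protocol fixes three things: the sole pre-treatment KCCQ is at screening, no maximum interval to the first fraction is stated, and there is no control group. It follows that untreated change between Visit 1 and Visit 4, in either direction, can be counted in the KCCQ change.

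The size cannot be derived from the documents. The figures above rest on an assumed SD of 15 to 20 points, an assumed drift of 5 to 10 points, an assumed number of drifting patients and an assumed test. The share of patients who drift moves the result more than any other assumption. If few are screened close to an acute episode, the effect on the false-positive rate is small. Neither a certain bias in favour of radiotherapy nor any effect on the safety conclusions is shown. This is a cheap improvement worth making, not a demonstrated error.

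**What to change.** 1. Add the KCCQ at Visit 4, before the first fraction, where the symptom questionnaire is already scheduled, and make it the baseline for the KCCQ change.
2. Keep the Visit 1 KCCQ. Report the Visit 1 to Visit 4 change, with the interval in days, beside the main result as an estimate of untreated drift.
3. Amend sections 9.5 and 9.6 and Appendix A. In the same amendment, reconcile the KCCQ at Visits 7 to 9 in the section 9.6 text with Appendix A, which marks only Visit 9 after treatment.

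Cost: about 13 extra 23-item questionnaires at a visit already held, plus the schedule amendment. Limit: a Visit 4 baseline takes out drift before treatment only. Regression to the mean and natural recovery after Visit 4 remain, and without a control group the report should say so.
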